### Design

2.1

The study is a multicenter observational cohort trial lasting 2 years in 5 locations, including Longhua Hospital affiliated to Shanghai University of TCM, Shuguang Hospital affiliated to Shanghai University of TCM, Yueyang Hospital of integrated Chinese and Western Medicine, Zhejiang Provincial Hospital of TCM, and Fudan University Shanghai Cancer Center. All the eligible TNBC patients are divided into 2 cohorts: TCM exposure group and nonexposed group, according to whether taking TCM treatment (Fig. 1). Participants in the nonexposed group receive preoperative chemotherapy and/or radiotherapy, as well as postoperative biological agents after surgery, according to the National Comprehensive Cancer Network (NCCN) Breast Cancer Treatment Guidelines. Participants in the TCM exposure group receive TCM combined with Western medicine treatment. TCM treatment is based on syndrome differentiation by inspection, listening and smelling, interrogation, pulse-taking, and palpation, and then provide the most appropriate decoction.

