### Sample size

2.2

Considering the results of the study at MD Anderson Cancer Center in foreign countries^[15]^ showed that the 3-year survival rate of TNBC patients was significantly shorter than that of non-TNBC patients (74% vs 89%, *P* < .01), as well as the lost rate of 20%, the sample size (N) is calculated by the following formula: 
[figure not shown]

*P*_0_ means the recurrence and metastasis rate of the nonexposed group; *P*_1_ represents the recurrence and metastasis rate of the TCM exposure group, *P*_1_ = RR × *P*_0_, where RR is the relative risk caused by exposure factors.

This study assumes that α = 0.05 and β = 0.10. According to the related study, the rate of recurrence and metastasis was 12% in the TCM group and 33.33% in the western medicine treatment group, respectively. The relative risk (RR) of TCM intervention was that RR = 12%/33.33% = 0.36. Domestic and foreign data showed that the 2-year recurrence and metastasis rate of TNBC patients was 17%, so *P*_0_ = .17, *P*_1_ = RR × *P*_0_ = 0.06.

Substituting the formula, the calculated amount of each group is as follows: 

Considering the 20% of drop rate, the confinement factor in different hospitals increased by 10% of the sample size, that is, at least 249 (N ≥ 249) cases should be observed in each group. Then, combined with the study period and the target population distribution of the study unit, 310 cases should be included in the Chinese medicine and Western medicine groups, respectively, in this study.

Before the research, investigators are responsible for the introduction the clinical research related matters and the records of the baseline data, then all participants sign the informed consent form. Patients in the TCM exposure group take Chinese medicine (San Yin Decoction) as well as original Western medicine, while patients in the nonexposed group only receive Western medicine treatment. The study will be performed during 2 years, and all results are recorded according to the Case Report Form (CRF).

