#### Secondary outcomes

2.3.2

Secondary outcome are as follows:

1)TCM symptom: based on the “Chinese Medicine New Drug Clinical Research Guidelines (Trial)” (China Medical Science and Technology Press, 2002), the investigators evaluate the TCM symptom every 3 months using scoring method as summarized in Table 1. The efficacy is assessed at 3 levels: significant improvement, the integral value after treatment decreased by ≥ 70% than the integral value before treatment; partial improvement, the integral value after treatment decreased by ≥ 30% than the integral value before treatment; no improvement, before and after treatment without change or after treatment integral value than the integral value before treatment decreased by < 30%. All results are recorded in the CRF table;2)Karnofsky Performance Status (KPS): the KPS ranking^[16]^ runs from 100 to 0, where 100 is “perfect” health and 0 is death. Practitioners occasionally assign performance scores in between standard intervals of 10. The investigators evaluate the KPS score every 3 months using scoring method as summarized in Table 2. The efficacy is assessed at 3 levels: improved, KPS score increased > 10 points and maintained for more than 4 weeks; stable, KPS score no significant change; worsening, KPS score reduced by < 10 points. All results are recorded in the CRF table;3)ECOG score: the Eastern Cooperative Oncology Group (ECOG) score (published by Oken et al in 1982),^[17]^ runs from 0 to 5, with 0 denoting perfect health and 5 denoting death. The investigators evaluate the ECOG score every 3 months, and the efficacy is assessed using scoring method as summarized in Table 3. All results are recorded in the CRF table;4)European Organization for Research and Treatment of Cancer (EORTC) Breast-Cancer-Specific Quality of Life Questionnaire (EORTC QLQ-BR23)^[18]^: This questionnaire focuses on physical condition and the quality of life of all participants. The investigators evaluate the score every 3 months, and the efficacy is assessed using scoring method. All results are recorded in the CRF table;5)Clinical indicators: Tumor markers (CEA, CA153, CA125, CA199), immune function evaluation (NK, CD3, CD4, CD8, CD4/CD8), chest computed tomography (CT)/magnetic resonance imaging (MRI), and abdominal B-ultrasound are detected to monitor whether there is the tumor recurrence and metastasis. All the participants perform tumor markers check and immune function evaluation every 3 months, as well as chest CT/MRI and ECT every 6 months;6)Safety indicators are carried out to assess drug safety and whether the participants have any adverse reactions. Blood, urine, and feces routine, liver and kidney function, abdominal B-ultrasound, and electrocardiogram are performed every 3 months. If the investigators find any adverse events (AEs), the event should be assessed according to the WHO acute and subacute side effects of the performance and indexing criteria for assessment. All results are recorded in the CRF table.

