### Statistical analysis

2.6

SPSS 18.0 (SPSS, lnc., Chicago, IL), Stata10.0 (StataCorp, College Station, Texas), and other statistical software are used for data analysis with a 2-sided significance level of 0.05, the point estimate, and 95% confidence interval. If the data obey the normal distribution and the variance is homogeneous, data are expressed as the number of cases (n) and the mean ± standard deviation (SD). Before and after treatment at multiple time points, measurement data using repeated measurement of variance analysis and multiple variance analysis are expressed as median (M), minimum (min), and maximum (max). The Kruskal–Wallis H test is used to compare the data between the 2 groups. The numerical variables are measured at multiple time points before and after treatment, and the generalized estimating equations or mixed effect models are used for the classification and sorting variables. If the analysis index is disordered using χ^2^ test, the analysis index is ordered with rank sum test, the 2-way ordered attribute of different data using linear χ^2^ test, and rank sum test. The survival rate is calculated by Kaplan–Meier method (K-M method), and the survival curve is drawn. Multivariate data are analyzed using multiple linear regression analysis, COX regression analysis, trend testing, and so on.

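### Cohort may be confounded with hospital, yet the two-group test named for measured outcomes has no hospital stratum and the only stated allowance for hospital differences is a 10% larger sample

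*Protocol article*

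**What the plan says.** All of the following is in the protocol article.

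- **Sites (section 2.1).** "The study is a multicenter observational cohort trial lasting 2 years in 5 locations". They are "Longhua Hospital affiliated to Shanghai University of TCM, Shuguang Hospital affiliated to Shanghai University of TCM, Yueyang Hospital of integrated Chinese and Western Medicine", then "Zhejiang Provincial Hospital of TCM, and Fudan University Shanghai Cancer Center". That makes four TCM or integrated-medicine hospitals and one cancer centre.
- **Cohorts (section 2.1).** Patients form a "TCM exposure group and nonexposed group, according to whether taking TCM treatment". No randomisation, and no matching within hospital, is described. Enrolment by site and cohort is not given.
- **Laboratory outcomes (section 2.3.2, item 5).** Four tumour markers and five immune measures are secondary outcomes: "Tumor markers (CEA, CA153, CA125, CA199), immune function evaluation (NK, CD3, CD4, CD8, CD4/CD8". They are repeated every 3 months, and together with imaging they "are detected to monitor whether there is the tumor recurrence and metastasis". The item does not say whether testing is local or central, or whether values, changes or categories are analysed.
- **Analysis (section 2.6).** "The Kruskal–Wallis H test is used to compare the data between the 2 groups". Repeated-measures analysis of variance, generalized estimating equations, mixed models, and multiple linear and Cox regression are also named. No covariate is listed for any of them.
- **Hospital differences (section 2.2).** The one mention is that "the confinement factor in different hospitals increased by 10% of the sample size".

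**The concern.** In a nonrandomised cohort study, anything that differs between hospitals biases the cohort comparison if the two cohorts come from the hospitals in different proportions. Here an uneven mix is plausible. The Background says that most postoperative TNBC patients in China have had some TCM, and four of the five sites are TCM or integrated-medicine hospitals, yet 310 nonexposed patients are needed. The cancer centre is a natural source for them.

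A two-group Kruskal-Wallis test compares the cohorts across all hospitals together and has no place for a hospital term. A larger sample narrows the interval around a biased difference. It does not move the difference towards zero, and it makes a spurious one more likely to reach significance.

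The laboratory outcomes show the problem most clearly. If hospitals run their own assays, a difference in calibration or cell-counting method between laboratories becomes a difference between cohorts. Since the Background lists immune regulation among the benefits of TCM, such a difference could be read as efficacy.

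**Working it through.** **1. The plan's own figure.** Section 2.2 gives at least 249 per group. Inputs are P0 = 0.17, RR = 0.36, P1 = 0.36 × 0.17 = 0.0612, two-sided α = 0.05 and β = 0.10. The standard two-proportion formula is

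n = [1.960 × √(2p̄(1−p̄)) + 1.282 × √(P0(1−P0) + P1(1−P1))]² / (P0−P1)², with p̄ = 0.1156.

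This gives 179.4, so 180 per group. Adding 20% loss and the 10% hospital allowance gives 180/0.8 × 1.1 = 247.5, or 180/0.8/0.9 = 250. The stated 249 is reproduced to rounding. It concerns recurrence and metastasis, and it shows that the hospital allowance enters only as a multiplier on n.

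**2. Bias in an unadjusted comparison of values.** Inputs:

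- From the document: 310 per group, two-sided 5% level.
- Assumed: a constant offset d between the cancer centre's laboratory and the other four, of 0.2 to 0.5 SD.
- Assumed: the share of each cohort at the cancer centre, s_E for exposed and s_N for nonexposed. Several mixes are shown because none is stated.
- Assumed: no true TCM effect.

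Formulas, in SD units:

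- Bias = d × (s_N − s_E)
- SE = √(2/310) = 0.0803
- False-positive rate = 1 − Φ(1.96 − bias/SE) + Φ(−1.96 − bias/SE)

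This is a z test on means, used as an approximation to the rank test.

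| s_E vs s_N | Bias, d = 0.2 | Bias, d = 0.5 | False-positive rate |
|---|---|---|---|
| 20% vs 20% | 0 | 0 | 5% |
| 10% vs 50% | 0.08 | 0.20 | 17% to 70% |
| 5% vs 60% | 0.11 | 0.275 | 28% to 93% |
| 0% vs 80% | 0.16 | 0.40 | 51% to over 99% |

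One line in full, for 5% vs 60% and d = 0.2: bias = 0.2 × 0.55 = 0.11; 0.11/0.0803 = 1.37; 1 − Φ(0.59) + Φ(−3.33) = 0.278.

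**3. Allowing for the planned 20% loss.** With 310 × 0.8 = 248 per group, SE = √(2/248) = 0.0898. The rates become about 15% to 61% (10% vs 50%) and 23% to 87% (5% vs 60%). The bias itself is unchanged. This also shows that a larger n raises the false-positive rate.

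**4. What would remove it.** If both cohorts occur within hospitals, a hospital stratum or fixed term removes a constant offset. So does within-patient change, or the group-by-time term, for a constant additive offset when each patient stays with one laboratory. A group main effect, or a rank test on values, keeps it.

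**The case against.** The strongest objection is that this is a condensed article. Laboratory arrangements and covariate lists are usually left to the full protocol or SAP, which are not shown. Section 2.6 lists no covariates for any model, so the absence of hospital is not a decision to exclude it. The regression and mixed models that it names could carry a hospital term, and a before/after analysis judged on group-by-time would already cancel a constant additive offset. The measures are secondary and described as monitoring for recurrence, while the main conclusions rest on PFS and OS.

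Much of this stands. A reader might infer that raw values from five local laboratories are pooled. The article does not say so: it is silent on local or central testing and on the form of the variable analysed. A reader might also infer that cohort and laboratory largely coincide, but without enrolment by site only a possible association can be claimed. Nor does it follow that all nine measures would be biased together. Five laboratories may differ in either direction and partly cancel, whereas the calculation treats four of them as identical.

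Two things are left. The article does not leave the between-group comparison open: it names a test that cannot take a hospital term. It also says how hospital differences are allowed for, and that allowance concerns precision rather than bias. Both are stated choices and can be judged as such. The article links linear regression to no particular outcome, describes the GEE and mixed models chiefly for categorical and ordinal variables, and does not say which contrast of the repeated-measures analysis is inferential.

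**Conclusion.** The point holds as one about hospital confounding in the stated analysis. Exposure is not randomised and may follow hospital, the named two-group test for measured outcomes has no hospital stratum, and the 10% enlargement cannot remove systematic bias. Tumour markers and lymphocyte subsets are the most exposed outcomes if testing is local.

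The size cannot be fixed from the documents. It runs from none, with an equal site mix, to a false-positive rate near 100% under extreme imbalance. The intermediate figures rest on an assumed constant offset, an assumed mix, no true effect and an unadjusted comparison of values. They illustrate the mechanism and do not estimate this trial's error rate.

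Since the outcomes are secondary and the remedy is cheap, this should be changed, but it does not by itself undermine the study. The same lack of a named hospital adjustment also applies to PFS and OS, whose bias is not quantified here.

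**What to change.** In section 2.6:

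1. State that cohorts are compared within hospital, either by a hospital-stratified rank test in place of the plain Kruskal-Wallis test, or with hospital as a fixed term in the regression, mixed or GEE model.
2. State that the inferential contrast for the tumour markers and immune measures is change from the patient's own baseline, or the group-by-time term, and not the raw level. This cancels a constant additive offset only if a patient's serial samples stay with one laboratory. If the full protocol already provides for this, a cross-reference is enough.

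The 10% allowance in section 2.2 can stay as a margin for precision, but should not be presented as dealing with differences between hospitals.

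The cost is wording only, with no extra tests or visits. The statistical price is that a hospital contributing almost only one cohort adds little to a within-hospital comparison, so intervals widen. If the cohorts hardly overlap within hospitals, the adjusted result will be imprecise. Tabulating enrolment by hospital and cohort would show this early.

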
**Table 1 T1:**
[figure not shown]
TCM symptom assessment table.

**Table 2 T2:**
[figure not shown]
KPS symptom assessment table.

**Table 3 T3:**
[figure not shown]
ECOG symptom assessment table.

All the participants are followed by telephone and outpatient visits, and the investigators track the situation of each participant (Table 4).

**Table 4 T4:**
[figure not shown]
Schedule of enrollment and assessment.

### Study participants

2.4

All the clinical and pathological diagnoses are defined according to the Chinese Medical Association prepared the “clinical treatment guidelines- tumor volume.” On the basis of the 2002 American Cancer Society “AJCC breast cancer staging standards,” internationally recognized TNM staging, lymph node biopsy, pleural effusion, and other tests were used to confirm the recurrence of metastatic lesions.

### Inclusion and exclusion criteria

2.5

Participants’ inclusion criteria are as follows: The primary BC after surgical treatment, the pathological diagnosis of breast epithelial tumors (BC), ER, PR, and Her-2 immunohistochemical results were negative; no recurrence of metastasis; KPS score ≥ 60 points; aged 18 to 75 years (including 18 and 75 years); no serious organic or functional disorders, no drugs, and food allergy; and willing to receive treatment, observation, and inspection.

Participants’ exclusion criteria are as follow: do not meet the inclusion criteria; patients expected to survive < 6 months; complicated with cardiovascular and cerebrovascular, liver, kidney, hematopoietic system of serious primary disease, and mental illness; breastfeeding, pregnancy, or women preparing for pregnancy; allergies and allergies to a variety of drugs; and participating in other drug subjects.

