#### Primary outcomes

2.3.1

Primary outcomes include progression-free survival (PFS): the time from treatment to disease recurrence or death due to disease progression; and OS: the time from the beginning of treatment to death due to any cause. These 2 indicators are calculated at the end of the trial.

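### No entry window after surgery or adjuvant treatment is stated, so if the two cohorts enter at different points after surgery, PFS and OS are confounded, in either direction

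*Protocol article*

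**What the plan says.** Section 2.5 (Inclusion and exclusion criteria) anchors entry to surgery without a time limit: "The primary BC after surgical treatment, the pathological diagnosis of breast epithelial tumors (BC), ER, PR, and Her-2 immunohistochemical results were negative; no recurrence of" … From the recurrence condition on, the same list reads "no recurrence of metastasis; KPS score ≥ 60 points; aged 18 to 75 years". The exclusions cover prognosis ("patients expected to survive < 6 months"), serious comorbidity, pregnancy and breastfeeding, allergy, and participation in other drug studies. None of them refers to time since surgery, chemotherapy or radiotherapy.

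Section 2.1 (Design) forms the cohorts by exposure: "TCM exposure group and nonexposed group, according to whether taking TCM treatment". Section 2.3.1 defines PFS as "the time from treatment to disease recurrence or death due to disease progression", and OS likewise starts when treatment begins. Neither is tied to surgery or diagnosis.

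Section 2.2 (Sample size) takes its control rate from outside data: "Domestic and foreign data showed that the 2-year recurrence and metastasis rate of TNBC patients was 17" per cent.

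Section 2.3.2 grades the TCM symptom score by change from the patient's own starting score ("significant improvement, the integral value after treatment decreased by ≥ 70% than the integral value before treatment") and grades KPS by a change in points.

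Section 2.6 lists Kaplan–Meier and Cox regression. It names no matching, stratification or covariate for time since surgery.

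**The concern.** As written, a patient a few weeks after surgery and a patient who has been recurrence-free for years both qualify. The second has already come through part of the risk period. In a randomised trial such a mix would balance on average. Here exposure is whatever the patient happens to take, so nothing makes the two cohorts enter at the same point in the disease course. If they do not, a difference in recurrence or survival may reflect where patients stood at entry and not TCM.

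This is a different matter from which date starts the clock. Timing both cohorts from enrolment would still compare different stretches of the risk period.

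A second, separate route concerns outcomes graded by change. A patient who enters just after surgery or during chemotherapy has room to improve simply by recovering. If one cohort holds more such patients, its symptom and KPS grades improve more for that reason alone.

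**Working it through.** **The plan's own figure.** From section 2.2: P0 = 0.17, RR = 12/33.33 = 0.36, P1 = 0.36 × 0.17 = 0.0612, α = 0.05 (two-sided, section 2.6), β = 0.10. With the mean proportion p̄ = 0.1156, n = 2 × p̄(1 − p̄) × (1.960 + 1.282)² / (0.17 − 0.0612)² = 181.5 per group. Then 181.5 / 0.80 × 1.10 = 249.6, in line with the stated 249. The sample size arithmetic is not in dispute. It supplies the 17% and the planned 310 per group used below.

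**Illustration of the recurrence bias.**

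Input from the document: a two-year recurrence rate of 17%, here applied to early entrants.

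Assumptions not in the document: no TCM effect; a late-entrant hazard of one half or three quarters of the early hazard; 50% or 70% late entrants in the TCM cohort against 20% in the nonexposed cohort.

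- Early hazard: −ln(0.83)/2 = 0.0932 per year.
- Late two-year risk at half hazard: 1 − exp(−0.0932) = 8.9%.
- Late two-year risk at three-quarters hazard: 1 − exp(−0.75 × 2 × 0.0932) = 13.0%.
- Cohort risk = (share late × late risk) + (share early × 17%).

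| Late hazard | Late share, TCM v nonexposed | Two-year risk, TCM v nonexposed | Spurious RR | Chance of a false significant result for TCM, 310 per group |
|---|---|---|---|---|
| half | 50% v 20% | 12.9% v 15.4% | 0.84 | 14% |
| three quarters | 50% v 20% | 15.0% v 16.2% | 0.93 | 6% |
| half | 70% v 20% | 11.3% v 15.4% | 0.74 | 32% |
| three quarters | 70% v 20% | 14.2% v 16.2% | 0.88 | 10% |
| any | equal | equal | 1.00 | 2.5% (nominal) |
| same as early | any | 17% v 17% | 1.00 | 2.5% (nominal) |

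The last column is a normal approximation for comparing two proportions. For the first row: difference 0.0243, null standard error 0.0280, so (0.0243 − 1.96 × 0.0280)/0.0280 ≈ −1.09, and Φ(−1.09) ≈ 0.14.

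**Reversed imbalance.** If the nonexposed cohort is the one with more late entrants, the same figures invert: RR 1.19 and 1.08 for 50% v 20%, and 1.36 and 1.14 for 70% v 20%. The bias then runs against TCM.

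**Change-graded outcomes.** No figure can be derived, but the direction can be reasoned out. Recovery common to both cohorts cancels in a between-group comparison. What does not cancel is a difference in treatment phase at entry, and that favours the cohort that enters nearer to its treatment. In the table above that is the nonexposed cohort, so an imbalance that flatters TCM on recurrence would tend to disfavour it on the symptom and KPS grades.

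**The case against.** The strongest reply is that this is one possible confounder in an observational cohort and that every number attached to it is assumed. The late fractions, the hazard ratio and the direction of imbalance have no source in the document, and mixing alone does no harm to the comparison. That is right, and it is why the point is conditional on the cohorts differing.

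Second, the plan may limit entry implicitly. Sections 2.1 and 2.2 describe perioperative guideline treatment and TCM added to existing Western treatment, which a survivor years past all therapy fits poorly. This makes extreme mixes less likely, but it is a description and not an eligibility rule. Figure 1 and Table 4 are not shown, so a window stated there cannot be ruled out.

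Third, the choice of covariates and strata commonly belongs in an SAP, which is not shown. That stands for the analysis details. Who may enter is an eligibility matter, however, and section 2.5 presents its lists as the criteria.

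Several stronger readings are tempting and are not supported:

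- A reader might infer that disease course and recovery together would pass for a TCM benefit. Under one and the same imbalance they tend to pull in opposite directions.
- A reader might infer that TCM patients enter later. The document does not say how exposed patients are found.
- A reader might infer that late entrants push the event rate below the planned 17%. Section 2.2 says only that the rate is for TNBC patients; their time since surgery is not given.
- A reader might extend the recovery bias to QLQ-BR23 and the immune counts. Section 2.3.2 gives explicit change-based grades only for the symptom score and KPS.

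**Conclusion.** The point holds in conditional form. The shown text states no interval since surgery or adjuvant treatment, and neither the allocation nor the named analysis aligns the cohorts on it. If the cohorts differ in time since surgery at entry and the hazard falls with that time, PFS and OS are confounded, with the direction set by which cohort enters later.

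The illustrated spurious RR is 0.74 to 0.93 when the TCM cohort enters later, well short of the planned effect of 0.36. It is 1.0 with an equal mix or a constant hazard. This size rests on the assumed late fractions and hazard ratios. The document shows neither that the imbalance exists nor which way it runs.

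The possible bias in the symptom and KPS grades is a separate consequence, of unknown size, and it need not agree in sign with the recurrence bias. The matter should be dealt with because the remedy is cheap and the comparison is not randomised.

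**What to change.** 1. For every patient, including those recruited since January 2017, record the date of surgery and the dates of last chemotherapy and radiotherapy, and tabulate time since surgery at entry by cohort.
2. Specify that the primary Cox comparison of PFS and OS is stratified by, or adjusted for, time since surgery at entry, with the strata or functional form fixed before outcomes are compared.
3. Adjust the change-from-baseline outcomes for treatment phase at baseline.
4. For patients not yet recruited, state in section 2.5 one common entry interval after surgery for both cohorts, its length set by the sponsor.

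Cost: items 1 to 3 mean retrieving treatment dates from the medical record (not only the surgical record) and slightly more analysis. Item 4 costs more. It slows accrual and changes the enrolled population partway through recruitment, so patients entered before and after the change would need to be distinguishable in the analysis. If the sponsor judges that cost too high, items 1 to 3 still deal with most of the problem, provided the cohorts overlap enough in time since surgery to be compared.
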